### 2.6. Sample Size

The calculation of the sample size has been carried out with the data analysis program EPIDAT https://www.sergas.es/Saude-publica/EPIDAT?language=es (accessed on 4 August 2023). For the calculation, a clinical variation of 2 and a standard deviation of 1 have been considered. A statistical power of 80% and a significance level of *p* < 0.05; 95% confidence level. The minimum size would be a sample of 128 subjects (64 in each group randomly distributed). Considering that the loss rate could be 30%, the final size should be 84 subjects in each group. The total sample size should be 168 subjects.

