### 2.7. Statistical Analysis

The description of data will be calculated using the percentages and frequencies of the qualitative variables and for the quantitative variables, the standard deviation and the mean. In addition, in case of presenting high deviations, the measures of central tendency would be calculated, as is the case of the mean, median or mode. All this will be carried out in frequency distribution tables of different categories, using SPSS (IBM SPSS Statistics: V.28, USA).

It is intended to compare the dependent variables with the independent ones. The Kolgorov–Smirnof test (the adjustment to the normal of the distribution) will be used to check the normality of the quantitative variables; in the event that they follow a normal distribution, the following techniques would be used: linear regression or Pearson correlation for the comparison of quantitative variables, chi-square (X^2^) to compare qualitative variables and Student’s *t* or ANOVA to compare qualitative with quantitative variables. In the event that they do not conform to the normal, it will be calculated according to the case; the Wilcoxon test, the Kruskal–Wallis test, and the Mann–Whitney test.

To determine that the supposed differences between control group and experimental group are not due to a random error, but to a real difference, in the bivariate analysis a hypothesis test will be carried out. The significance level of p shall be 0.05.

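### Section 2.6 is internally inconsistent: a difference of 2 with SD 1 needs about 6 children per group, while the stated 64 per group corresponds to a standardised difference of 0.5

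*Protocol article*

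**What the plan says.** The whole calculation is in one paragraph of the protocol article, section 2.6 (Sample Size). It was done in EPIDAT, and the effect assumption reads: "For the calculation, a clinical variation of 2 and a standard deviation of 1 have been considered". No outcome or unit is attached to either number. The error rates follow: "A statistical power of 80% and a significance level of" p < 0.05, with a "95% confidence level". The result is given as: "The minimum size would be a sample of 128 subjects (64 in each group randomly distributed"). Loss is then allowed for: "Considering that the loss rate could be 30%, the final size should be 84 subjects in each group", which makes 168 in total.

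Section 2.7 (Statistical Analysis) repeats the level: "The significance level of p shall be 0.05". It names Student's t or ANOVA for comparing groups on a quantitative variable, with Mann–Whitney among the fallbacks if normality fails. No other part of the article gives a different effect size or SD.

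**The concern.** A difference twice the SD is an extremely large effect and should call for a very small trial. A requirement of 64 per group is what one expects for a moderate effect of half an SD. Inputs and result stand in the same paragraph, and both cannot be right.

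This paragraph is the article's only statement of the effect the trial is meant to detect. Section 2.4.2 lists quantitative outcomes in degrees, millimetres, pain-scale points and index scores, and nothing says which of them the 2 and the 1 belong to. A reader therefore cannot reproduce the size. Nor can a reader judge a later result against the target: an observed effect of about 0.5 SD would be what 64 per group can detect, yet only a quarter of the effect as written. Someone who takes the inputs at face value would also ask why 168 children are enrolled when about 12 evaluable ones would be enough.

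**Working it through.** **Inputs.** From section 2.6: difference 2, SD 1, power 80%, significance level 0.05, two equal groups. Two readings are assumed. Clinical variation is taken as the between-group difference in means. The test is taken as two-sided, which the article does not state but which fits its 95% confidence level.

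**Formula.** Normal approximation, per group: n = 2 × (z₀.₉₇₅ + z₀.₈₀)² / d², where d = difference / SD. Here (1.960 + 0.842)² = 7.849. The exact version uses the noncentral t distribution with 2n − 2 degrees of freedom.

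**Attempt to reproduce 64 from the stated inputs.** d = 2/1 = 2.0.
- Normal approximation: 2 × 7.849 / 4 = 3.9, so 4 per group.
- t-test: n = 5.09, so 6 per group (power 0.79 at 5, 0.88 at 6), or 12 children in total.

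The figure of 64 is not reproduced.

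**Other readings, all with difference 2 and SD 1.**

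| Variant | n per group |
|---|---|
| One-sided 5% | 4 |
| 90% power (normal) | 6 |
| 95% power (normal) | 7 |
| Bonferroni over 100 tests | 10 (normal), 13 (t) |
| Mann–Whitney at efficiency 0.864 | about 5 to 7 |
| SD of 1 taken per measurement, SD of a difference 1.414 | 8 (normal), 9 (t) |
| Non-inferiority with margin 2 | 4 |

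None comes near 64.

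**Reverse calculation: what does 64 per group detect?**
- At d = 0.5: 2 × 7.849 / 0.25 = 62.8, so 63 by the normal approximation. The t-test gives n = 63.77, so 64, with power 80.1%.
- The smallest d with 80% power at 64 per group is 0.499.
- Ratio of the stated effect to this: 2.0 / 0.499 = 4.0.
- Ratio of sizes: 64/6 = 10.7 by t-test, 64/4 = 16 by the normal approximation.
- At 64 per group, power for d = 2.0 is effectively 100%.

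Any difference and SD in the ratio 1:2 gives 64, for example 1 and 2, or 2 and 4.

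**What enrolment of 84 per group delivers if 0.5 SD was the target.** With the stated 30% loss, 84 × 0.70 = 58.8 evaluable. Power at d = 0.5 is 76.1% with 58 and 76.8% with 59. The effect detectable with 80% power is 0.525 SD with 58 and 0.520 SD with 59. The figure of 84 is 64 × 1.3 = 83.2 rounded up; to end with 64 after 30% loss takes 64 / 0.70 = 91.4, so 92 per group.

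**The case against.** The arithmetic itself has no answer: the sentence is complete and legible, and an article that condenses a longer protocol may leave detail out but should not print figures that disagree. The fair objections concern how far the conclusion goes.

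- **Which number is wrong is not shown.** A reader might infer that the two inputs were simply interchanged. The exact match at 0.5 makes that plausible, but a difference of 2 with SD 4 fits equally well, and nothing in the article says what was entered. This objection stands.
- **Clinical variation is not defined.** Taking it as the between-group difference is the natural reading, but it is a reading. This stands as a stated assumption.
- **The trial is not shown to be too small.** A reader might infer an underpowered trial. For the effect as written, power is close to 100%; for 0.5 SD, 64 evaluable per group is the right number. The mismatch alone does not support a charge of inadequate size. The modest shortfall after losses comes from the 30% allowance, not from the mismatch.
- **Correcting the inputs alone would not settle it.** One might think it enough to put in a difference and SD that yield 64 and leave the rest. That would be back-fitting, and it would credit the trial with 64 evaluable children per group, which 84 randomised with 30% loss does not deliver.

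**Conclusion.** The inconsistency is real and section 2.6 is wrong as written. Under a two-sided 5% test with 80% power, difference 2 and SD 1 require about 6 per group by t-test (4 by the normal approximation), not 64. The size of 64 matches a standardised difference of 0.5, so the stated effect and the effect the trial is sized for differ about fourfold. This rests on reading clinical variation as the between-group difference and on a two-sided test; none of the alternatives tried brings the result above 13 per group.

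The documents do not show which figure is in error, so interchanged inputs remain a conjecture. What is established is that the target effect can be neither reproduced nor interpreted. Since it is the only basis given for the sample size, it should be corrected.

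**What to change.** Rewrite the effect assumption in section 2.6 and keep enrolment at 168:

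1. Name the outcome that the calculation refers to, with its unit.
2. Report the difference and SD actually entered in EPIDAT, with their source, and state that the test is two-sided if it is. The values should come from the record of the calculation and not be chosen to return 64.
3. State what the size delivers:
   - If the target was 0.5 SD: 64 evaluable per group gives 80% power, but 84 randomised per group with 30% loss leaves about 58 to 59 evaluable, which gives about 76 to 77% power at 0.5 SD, or 80% power for about 0.52 SD.
   - If 2 and 1 are the true inputs: power exceeds 99%, and 168 children must be justified on other grounds.

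The cost is a few sentences and no change in enrolment. The only downside is that, in the first case, the stated power is slightly less favourable than the 80% now claimed.

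### The allowance for 30% loss was made by multiplying 64 by 1.3 instead of dividing by 0.7, so 84 per group leaves about 59 completers against the protocol's own minimum of 64

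*Protocol article*

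**What the plan says.** All the relevant figures are in section 2.6 (Sample Size) of the protocol article.

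- Inputs: "a clinical variation of 2 and a standard deviation of 1 have been considered", followed by "A statistical power of 80% and a significance level of" 0.05. Section 2.7 repeats the level: "The significance level of p shall be 0.05". Neither section says whether the test is one- or two-sided, and section 2.6 does not name the endpoint to which the 2 and the 1 belong.
- Base size: "The minimum size would be a sample of 128 subjects (64 in each group randomly distributed".
- Loss allowance: "Considering that the loss rate could be 30%, the final size should be 84 subjects in each group".
- Total: "The total sample size should be 168 subjects".

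The same 168 reappears in Appendix D as the number of orthoses budgeted. Section 2.6 does not show how the 30% was applied.

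**The concern.** A loss allowance has one purpose: after the foreseen loss, the number left for analysis should still reach the minimum. Here it does not. Taking 30% away from 84 gives fewer than 64, so the section contradicts its own minimum at the loss rate it names. The shortfall is too large to be rounding: the gap between 84 and the size that would work is 8 children per group, 16 in total.

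At stake is the justification of the number to enrol. A reader of section 2.6 would conclude that the trial can lose 30% of its children and still have 64 per group for analysis. It cannot.

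**Working it through.** **Inputs.** From section 2.6: minimum 64 per group, two equal groups, possible loss 30%, final size 84 per group, difference 2, SD 1, power 80%. The level of 0.05 is in sections 2.6 and 2.7. Section 2.7 names Student's t or ANOVA for comparing a quantitative variable between groups. Assumption: two-sided test.

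**Step 1. Reproduce the 84.**
- Multiplying: 64 × (1 + 0.30) = 83.2, rounded up to 84, and 2 × 84 = 168. This matches the protocol.
- Dividing: 64 / (1 − 0.30) = 91.4, rounded up to 92, and 2 × 92 = 184. This does not match. (Rounding on the total, 128/0.7 = 182.9, gives 183; equal groups need 184.)

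**Step 2. Completers at 30% loss.**
- 84 × 0.70 = 58.8 per group, about 59; 168 × 0.70 = 117.6 in total, about 118. The minimum is 64 and 128.
- Check of the alternative: 92 × 0.70 = 64.4, while 91 × 0.70 = 63.7 falls just short.

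**Step 3. Loss that 84 can absorb.** 1 − 64/84 = 20/84 = 23.8%.

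**Step 4. Does 64 follow from the printed inputs?** With the normal approximation, n per group = 2 × (1.960 + 0.842)² / d² = 15.70 / d², where d is the difference divided by the SD.
- As printed, d = 2/1 = 2: 15.70/4 = 3.9, so 4 per group. The t-test calculation gives 5.1, so 6.
- With d = 0.5: 15.70/0.25 = 62.8, so 63 per group. The t-test calculation gives 63.8, so 64.

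So 64 is the two-sided t-test answer for 0.5 SD, a value that the protocol does not state. It does not follow from 2 and 1. A one-sided test does not rescue it: the normal approximation again gives 4 per group for d = 2.

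**Step 5. Power, conditional on the effect (two-sided t-test, level 0.05).**

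| Per group | d = 0.5 (assumed) | d = 2 (as printed) |
|---|---|---|
| 64 | 80.1% | above 99.9% |
| 59 | 76.8% | above 99.9% |
| 58 | 76.1% | above 99.9% |

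Under d = 0.5 the loss is 80.1 − 76.8 = 3.3 to 80.1 − 76.1 = 4.0 percentage points. The effect detectable with 80% power rises from 0.50 SD at 64 per group to 0.52 SD at 59.

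**The case against.** A reader might infer more than this: that the trial fails to deliver its 80% power. The documents do not support that without a condition. Every figure of 76% to 77% rests on 0.5 SD, which is obtained by working backwards from 64. On the difference and SD actually printed, 59 completers per group would give power close to 100%. It is tempting to assume that the 2 and the 1 were swapped, since a difference of 1 with an SD of 2 reproduces 64, but nothing in the document shows this. This objection stands and removes any unconditional statement about power.

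Three further points are fair. Section 2.6 presents 30% as a loss that might occur, not as the expected rate, and below 23.8% loss the minimum of 64 is kept. Even under 0.5 SD the effect on power is small. And 92 rests on a base of 64 that has itself not been reconciled with the inputs, so it cannot yet be called the correct size of the trial.

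One might also argue that a baseline-adjusted analysis would make up the difference. Having 58 do the work of 64 needs a correlation r between baseline and outcome with 1 − r² = 58/64, so r is about 0.31. The protocol gives no correlation and ties the sample size to no endpoint, so this cannot be relied on.

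None of this repairs the loss step. Whatever base size is right, a 30% loss among those enrolled is allowed for by dividing by 0.7, and no other section supplies a correction.

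**Conclusion.** The loss allowance is wrong as written. At 30% loss, 84 per group leaves about 59, which is 5 short of the protocol's own 64. The size that keeps 64 at that loss is 92 per group. This part needs no assumption beyond a loss rate being a share of the children enrolled.

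The consequence for power is modest and conditional: about 3 to 4 percentage points, if 64 is indeed the number needed for 80% power (0.5 SD, two-sided t-test). This is a correction to the sample-size justification and not evidence that the trial is seriously underpowered. The mismatch between the printed inputs and 64 is the larger fault in the section, and until it is settled no power figure can be attached to either 84 or 92.

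**What to change.** 1. Reconcile the difference of 2 and SD of 1 with 64 per group: name the endpoint and its unit, say whether the test is one- or two-sided, and correct whichever figure is wrong.
2. If 64 stands, keep 168 and replace the loss sentence with text such as: *Enrolling 84 per group preserves 64 evaluable children per group for losses up to 23.8%; at 30% loss about 59 per group would remain. Keeping 64 at 30% loss would need 92 per group.* If the base size changes, divide the new figure by 0.7 and do not multiply it by 1.3.
3. Give power at the reduced number only with its effect size stated, for example about 76% to 77% with 58 to 59 per group for 0.5 SD, two-sided t-test, and only if step 1 confirms 0.5 SD.

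Restating the loss sentence needs no additional children and changes no procedure; the real work is step 1. If the sponsor prefers 92 per group, that means 16 more children, and the Appendix D line for 168 orthoses must change too. At the budgeted 1680/168 = 10 € each, 16 more cost 160 €.

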### 2.7. Statistical Analysis

The description of data will be calculated using the percentages and frequencies of the qualitative variables and for the quantitative variables, the standard deviation and the mean. In addition, in case of presenting high deviations, the measures of central tendency would be calculated, as is the case of the mean, median or mode. All this will be carried out in frequency distribution tables of different categories, using SPSS (IBM SPSS Statistics: V.28, USA).

It is intended to compare the dependent variables with the independent ones. The Kolgorov–Smirnof test (the adjustment to the normal of the distribution) will be used to check the normality of the quantitative variables; in the event that they follow a normal distribution, the following techniques would be used: linear regression or Pearson correlation for the comparison of quantitative variables, chi-square (X^2^) to compare qualitative variables and Student’s *t* or ANOVA to compare qualitative with quantitative variables. In the event that they do not conform to the normal, it will be calculated according to the case; the Wilcoxon test, the Kruskal–Wallis test, and the Mann–Whitney test.

To determine that the supposed differences between control group and experimental group are not due to a random error, but to a real difference, in the bivariate analysis a hypothesis test will be carried out. The significance level of p shall be 0.05.

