#### 2.4.1. Qualitative or Categorical Variables:

Gender: masculine or feminine.Pain: symptomatic or asymptomatic.Level of physical activity: high-low-nil.Double/simple heel rise test: Standing on toes with two legs/one leg for 25 repetitions. It will be considered positive if the participant is incapable due to fatigue or if when raising the calcaneus does not present a varus position [38].Supination resistance test: high-moderate-low. The patient is instructed to stand relaxed without any attempt to move the foot or lift the arch. The examiner’s fingertips are then placed plantar to the medial half of the navicular, and the examiner exerts a significant lifting force on the navicular. A normal foot will demonstrate subtalar joint supination with minimal lifting force. A pes valgus deformity will need extreme amounts of lifting force in order to produce little, if any, subtalar joint supination motion [40].Subtalar joint axis: Lateralized-neutral-medialized. The center of the neck of the talus should be located and marked to see the lateralized or medialized point, or if, on the contrary, it stops at the 2nd finger, which would indicate that it is neutral [36].Shoe wear at heel level: medial-center-lateral.Maximum pronation test: Positive or negative. The patient is asked to try pronate as much as possible; it is considered positive when performing the maneuver, the calcaneus cannot pronate more than 2° [41].Forefoot: adduction-neutral-abduction position [36].Foot posture index (FPI): Normal = 0 to +5; pronated = +6 to +9; highly Pronated = +10 to +12; supinated = −1 to −4 and highly supinated = −5 to −12. The six clinical criteria assessed: 1. palpation of the talus head; 2. lateral supra and inframalleolar curvature; 3. position of the calcaneus in the frontal plane; 4. prominence of the talonavicular region; 5. congruence of the internal longitudinal arch and 6. abduction/adduction of the forefoot with respect to the rearfoot. As we observe them, the following score is given: neutral = 0; clear signs of supination = −2; clear signs of pronation = +2 [33].Test of windlass: Positive or negative. It will be considered positive if, when performing dorsiflexion of the hallux, there is not supination of the foot, plantarflexion of the 1st ray, increase in the MLA and internal rotation of the tibia [39].Beighton scale: Hypermobility or normal. Subjects are rated on a 9-point scale, considering 1 point for each hypermobile site. These 9 points are: 1-hyperextension of the elbows (more than 10°), 2-passively touch the forearm with the thumb, having the wrist in flexion, 3-passive extension of the index finger to more than 90°, with the palm of the hand resting on the bed, 4-hyperextension of the knees (10° or more), patient in supine position and 5-flexion of the trunk forward touching the ground with the palms of the hands by bending without bending your knees. To be considered as hypermobile, it is required to have 4 points or more of the total of 9 [42].Podoscope: pronated-supinated-neutral [36].Pressure platform: maximum pressure zone, location of the center of gravity, gait progression line [43].

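### The test rules in section 2.7 ignore the order of supination resistance and let a normality test decide which measure is compared between the arms

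*Protocol article*

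**What the plan says.** Section 2.7 assigns chi-square "to compare qualitative variables", and linear regression, correlation, Student's t or ANOVA where quantitative variables are involved. A Kolmogorov–Smirnov test "will be used to check the normality of the quantitative variables". If they are not normal, Wilcoxon, Kruskal–Wallis or Mann–Whitney is used, according to the case. The rank tests are thus tied to quantitative variables that fail the check, and no ordered test is assigned to graded categories. For alpha the section states "The significance level of p shall be 0.05".

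Section 2.4.1 lists the qualitative variables. One is "Supination resistance test: high-moderate-low", with a description in which a normal foot supinates under little force and a flat foot hardly at all under great force. Another is "Subtalar joint axis: Lateralized-neutral-medialized". Foot Posture Index (FPI) and pain appear there as categories and again in section 2.4.2 as numbers. Supination resistance and subtalar axis appear only as categories.

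Section 2.6 sizes the trial on "a clinical variation of 2 and a standard deviation of 1", without naming the outcome.

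**The concern.** Two stated rules are at issue.

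- **Graded categories.** With three levels, chi-square spends 2 degrees of freedom and gives the same result however the levels are ordered. Section 3 expects improvement, which is a directional effect. For a scale that runs from worst to best, a test that uses the order concentrates on that direction with 1 degree of freedom.
- **Normality pre-test.** FPI is a sum of six item scores and therefore discrete. A Kolmogorov–Smirnov test can reject such a score because of its steps alone, even when its general shape is bell-like. Whether the arms are compared on means or on ranks then depends on the data and can change from one outcome to the next for no clinical reason. The between-arm measure is not fixed in advance.

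**Working it through.** **1. The plan's own figure.** Two-sided alpha 0.05 is assumed, since sidedness is not stated; power is 80%. Normal approximation per group: n = 2 × (1.96 + 0.8416)² × SD² / difference².

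- Difference 2, SD 1: 2 × 7.849 × 1 / 4 = 3.9, so 4 per group (6 by the exact t-test). The stated 64 is not reproduced.
- Difference 1, SD 2 (standardised effect 0.5): 2 × 7.849 × 4 / 1 = 62.8, so 63 (63.8 by the exact t-test, so 64). This matches.

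The mismatch in section 2.6 is a separate matter. Here I take 64 per group and a standardised effect of 0.5. With difference 2 and SD 1 as printed, every test has about 100% power and the choice of test costs nothing for that outcome.

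**2. Chi-square against an ordered test, in theory.** An effect that gives a 1-df test 80% power has non-centrality (1.96 + 0.8416)² = 7.85. The same non-centrality on 2 df gives 70.9%. To get back to 80%, the 2-df test needs a non-centrality, and hence a sample, about 1.23 times as large. This assumes that the whole effect lies in the ordered direction.

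**3. The same by simulation.** Three levels, 64 per group, proportional odds, 3,000 runs per case. Level splits and odds ratios are assumptions.

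| Split in one arm | Odds ratio | Chi-square | Linear-by-linear | Mann–Whitney |
|---|---|---|---|---|
| 33/33/33 | 2.0 | 45.5% | 56.3% | 56.3% |
| 33/33/33 | 2.5 | 69.3% | 78.9% | 79.3% |
| 33/33/33 | 3.0 | 83.7% | 89.9% | 90.2% |
| 20/30/50 | 2.0 | 44.4% | 55.8% | 55.7% |
| 20/30/50 | 2.5 | 70.3% | 79.1% | 79.4% |
| 20/30/50 | 3.0 | 85.8% | 91.8% | 91.8% |
| 10/20/70 | 2.0 | 37.5% | 47.5% | 48.3% |
| 10/20/70 | 2.5 | 63.0% | 71.8% | 73.1% |
| 10/20/70 | 3.0 | 81.8% | 87.8% | 89.3% |

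The gaps run from about 6 to 11 points. Each entry has a simulation standard error of up to √(0.25/3000) = 0.9 points, so I read the loss as roughly 5 to 10 points.

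**4. A change that is not one-directional.** With 33/34/33 against 20/60/20 (assumed), chi-square has 77% power and the ordered tests about 5%. The ordered test is better only where the levels have a worst-to-best order.

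**5. How often the pre-test rejects.** Normal scores rounded to whole numbers; the SDs are assumptions.

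| Values tested | SD | Lilliefors version | Uncorrected version |
|---|---|---|---|
| 84 | 1 | 100% | 100% |
| 84 | 2 | 96–98% | 24% |
| 84 | 3 | 60% | 2% |
| 128 | 1 | 100% | 100% |
| 128 | 2 | 100% | 57–62% |

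The article does not say which version is meant, and the answer can turn on it.

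**6. What the switch to ranks costs.** 64 per group, 2,000 runs per case, standardised effect 0.5 before rounding and floor effects in the first three rows.

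| Score (assumed) | t-test | Mann–Whitney |
|---|---|---|
| Whole-number, SD 2 | 80.6% | 78.6% |
| Whole-number, SD 1 | 78.8% | 77.0% |
| 1–10 pain score with floor | 74.6% | 73.9% |
| Skewed, scale change, with floor | 78.8% | 68.0% |

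In theory, at normality the rank test has efficiency 3/π = 0.955. So 64 per group acts like 64 × 0.955 = 61, and power is 78.3% against 80.1%. Type I error of the two-stage rule stayed at 4.7% to 5.9%.

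**The case against.** The strongest reply is that chi-square is valid for graded categories, and that an article may leave the test for each outcome to an analysis plan that is not shown. The first part stands: nothing here is invalid. The second does not settle the matter, because section 2.7 states both rules and nothing in the article limits them.

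Four stronger readings are tempting and are not supported.

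- **That both rules lose material power.** The pre-test costs about 1 to 2 points or less in the normal-like and floor-limited cases, and more only in one assumed skewed case. The objection to it is the unfixed measure.
- **That every three-level outcome needs an ordered test.** Subtalar axis, forefoot and podoscope have neutral in the middle. If feet move to neutral from both ends, an ordered test can lose nearly all its power (step 4). FPI class is covered by the numerical score, and binary outcomes are unaffected.
- **That the trial was sized on a whole-number score with SD 1.** Section 2.6 names no outcome. Whole-number recording of pain is likewise an assumption.
- **That readers would get p-values without a mean difference, or could not see the direction of change.** Section 2.7 commits to means and SDs, and to percentages and frequencies, so both can be read from the descriptive tables.

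**Conclusion.** The point holds in a limited form and is minor. For supination resistance, the chi-square rule discards the order and costs roughly 5 to 10 points of power at 64 per group. That rests on a shift in one direction, odds ratios of 2 to 3 and the assumed level splits. The trial is not shown to be sized on this outcome. The pre-test leaves the choice between a mean and a rank comparison to the data. For a discrete score such as FPI, rejection ranges from near certain to rare, depending on the SD and the version of the test. No text in the article fixes the measure otherwise. The gain from repairing this is a prespecified, uniform effect measure, with little change in power.

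**What to change.** Change the wording of section 2.7 before any unblinded data are seen:

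- Use a test that respects order (linear-by-linear, Mann–Whitney or proportional odds) for supination resistance and any other category with a clear worst-to-best order.
- Keep chi-square for binary or unordered categories and for those with neutral in the middle (subtalar axis, forefoot, podoscope).
- Analyse FPI as its numerical score.
- Drop the normality pre-test. For the quantitative outcomes, prespecify a between-arm mean difference with 95% CI from a linear model adjusted for the baseline value, which section 2.5 already has measured. Keep the rank test as sensitivity analysis.

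The cost is wording only: no new data are needed, and the methods are available in the named software. There are two small downsides. The ordered test has less power for a change that is not one-directional. For heavily skewed or floor-limited outcomes such as pain, the mean comparison may be less efficient than the rank test, although in the one skewed case simulated here the rank test did worse.
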